#### d) List of non-reportable adverse events

Not applicable.

#### e) Time period in which the principal investigator shall report all adverse events and device deficiencies to the sponsor

We ensure that any event as referred to Article 80(2) will be fully recorded by the investigators, manufacturer or other parties, and immediately notified by the sponsor to all competent authorities (including FAMHP) by using the European form in a timely manner.

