### 3. Justification for the design of the clinical investigation

A first clinical study, led by the VUB, has been conducted with the LUNARIS® Demonstrator. The complete protocol (B.U.N. 143201526629) has been approved by the medical Ethics Committee of the University Hospital of the VUB.

In this study, forty-two participants completed the protocol assessing performance and functional mobility with their current prosthesis and the LUNARIS® Demonstrator. Subjective measures indicated the added value of this device, while overall task performance and intensity of effort did not differ between the LUNARIS® Demonstrator and the current prosthesis. The familiarisation time only lasted between one and two hours, which was not enough to obtain significant results between the LUNARIS® Demonstrator and the current prosthesis of the user [1].

In addition, a systematic review about therapeutic benefits of lower limb prosthesis was performed in 2021. It could be concluded that no studies investigating the long-term therapeutic benefits of performing daily activities with passive, quasi-passive and active ankle-foot prostheses in people with unilateral lower-limb amputation were found, highlighting a gap in the literature [2].

Lastly, further investigations (B.U.N. 143201526629 - Amendment) unravelling both acute and more prolonged adaptations were conducted to evaluate the LUNARIS® Demonstrator. This study revealed a potential long-term benefit of recovering a gait pattern of able-bodied persons after a few months of familiarisation. We hypothesised that it might be a consequence of the high flexibility of the LUNARIS® Demonstrator [3].

As a result, this study aims to demonstrate that doing the rehabilitation with the LUNARIS® may allow the user to recover a gait pattern closer to the one of able-bodied person and that brain plasticity will be less impacted when walking with the LUNARIS® than with another rigid prosthetic device. Studying the effect of the LUNARIS® during rehabilitation could be a great opportunity to investigate the rehabilitation with an articulated ankle prosthesis and the long term benefits of the LUNARIS®.

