### b) Exclusion criteria for subject selection

- Having metal implants
- Bilateral or additional upper-limb amputation
- Diabetic cause of amputation
- Neurological disorders
- Excessive stump pains and wounds

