### 14. Adverse events, adverse device effects, and device deficiencies

#### a) Definition of adverse events and adverse device effects

There are no disadvantages or risks associated with this research. Moreover, previous experiments with the Talaris Demonstrator (the LUNARIS® prototype, registered on B.U.N. 143201526629) have shown that there is a high willingness and motivation from the participants to participate in the experiments and no side or adverse effects were reported. Risks associated with the investigated medical device are reported in the Risk Management File.

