#### c) Definition of serious adverse events

There are no serious adverse events anticipated that will lead to death, injury, permanent impairment or deterioration in health anticipated for this clinical investigation and use of medical device.

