#### h) List of foreseeable adverse events and anticipated adverse device effects

The LUNARIS® is a CE-marked medical device. Therefore, a risk analysis has been performed according to ISO 14971 to ensure that risks associated with the device are identified, evaluated and controlled.

The risk analysis shows that any residual risks which may be associated with the device are acceptable, when weighed against the benefits of the intended use to the lower-limb amputee, and compatible with a high level of protection of health and safety.

i) Emergency contact details for reporting serious adverse events and serious adverse device effects

The principal investigator can be contacted in case of emergency for the reporting of serious adverse events.

The manufacturer can be contacted in case of emergency for the reporting of serious adverse device effects.

j) Information regarding the Data Monitoring Committee

Data will be analysed by the co-investigator(s) and controlled by the principal investigator in assignment of the sponsor. The DMC is the Vrije Universiteit Brussel, [name].

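### Section 14 promises a rule for all adverse events and device deficiencies, but its only recording commitment covers an unexplained legal class of events, and it defines none of its safety terms

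*Protocol*

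**What the plan says.** The heading of Section 14 e sets a wide scope: "Time period in which the principal investigator shall report all adverse events and device deficiencies to the sponsor". The text beneath it is narrower: "We ensure that any event as referred to Article 80(2) will be fully recorded by the investigators, manufacturer or other parties". It goes on to say that the sponsor will immediately notify these events to all competent authorities. The same sentence stands under 14 f (adverse events) and 14 g (device deficiencies). Section 4 e has it too, and there alone names the Medical Device Regulation as the source of the article.

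Three headings in Section 14 announce definitions.
- 14 a, on adverse events and device effects, opens with "There are no disadvantages or risks associated with this research".
- 14 b, on device deficiencies, says that none have been reported so far.
- 14 c, on serious adverse events, says "There are no serious adverse events anticipated that will lead to death, injury, permanent impairment or deterioration in health".

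Section 14 d, headed "List of non-reportable adverse events", is marked not applicable. Section 14 h says that "any residual risks which may be associated with the device are acceptable", and Section 4 c says the same. Section 6.3 b excludes candidates with "Excessive stump pains and wounds".

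**The concern.** A site following Section 14 cannot tell what counts as an adverse event, a serious adverse event or a device deficiency. It also cannot tell whether a stump wound, a fall or a device fault should be recorded when no authority has to be notified. The heading of 14 e suggests that it should; the text beneath commits to recording only the Article 80(2) class.

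The gap matters because twenty people will learn to walk on the investigational foot and wear it for 24 weeks in all, alongside twenty on the comparator. Events that are not asked about at the time cannot be recovered later. If the report then lists few or no events, a reader cannot tell whether none occurred or nobody asked. Nor can the two feet be compared on harms such as residual-limb problems, which the protocol regards as serious enough to bar entry.

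**Working it through.** The protocol states no safety figure to reproduce, so the main check is textual.

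**1. Scope of the recording rule.** The heading of 14 e covers all events, and 14 d exempts none. The sentence under 14 e, 14 f and 14 g covers Article 80(2) events, which the sponsor notifies immediately to all authorities. There are two possible readings:
- If the class means every adverse event, each episode of stump soreness would need immediate notification to every authority.
- If it means only notifiable events, all others have no stated recording rule.

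The text is unworkable on the first reading and incomplete on the second. The documents do not settle which applies.

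**2. Definitions.** Section 14 a gives a statement of no risk, 14 b a report of no deficiencies to date, and 14 c an expectation of no serious events. None of them says what the term means.

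**3. Timing.** The heading of 14 e concerns investigator to sponsor. Its text concerns sponsor to authorities, and describes that notification as both immediate and merely timely. No investigator-to-sponsor limit is given.

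**4. Consistency on risk.** Sections 4 b and 14 a say there are none. Sections 4 c and 14 h allow for residual ones, and Section 6.3 d says potential ones will be explained before consent.

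**5. Whether another section fills the gap.**
- The visit schedules (6.1 d, 6.4 a) and planned analyses (7 b) contain no adverse-event item.
- Section 6.4 e offers contact by appointment, email or telephone, without a stated enquiry.
- H1 (5 d) predicts fewer falls, yet falls are not among the tests and endpoints in 6.1 e.
- Section 7 m has drop-outs recorded but leaves them out of the analyses. Someone who leaves because of a stump problem would not be in the comparison.

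**6. Scale, by illustration.** Planned exposure to LUNARIS is 20 × 24 = 480 participant-weeks; over both amputee groups it is 40 × 24 = 960. The protocol gives no event rate, so assume a per-person risk p of a non-serious event over 24 weeks. The chance of at least one among 20 users is 1 − (1 − p)^20.

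| Assumed p | Expected in 20 | Chance of at least one |
|---|---|---|
| 5% | 1 | 64% |
| 10% | 2 | 88% |
| 20% | 4 | 99% |
| 30% | 6 | over 99.9% |

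Even with full collection, zero events in 20 people would exclude only risks above 1 − 0.05^(1/20) = 13.9% (one-sided 95% limit). With 18 people, after the planned 10% drop-out, the limit is 1 − 0.05^(1/18) = 15.3%. If events are not solicited, a zero does not support even those limits.

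**7. Earlier experience.** The statement in 4 b and 14 a that no adverse effects were reported concerns a prototype. In the 42-completer study in Section 3, "The familiarisation time only lasted between one and two hours". If the statement rests on those 42 people (an assumption), 0 of 42 is compatible with a risk up to 1 − 0.025^(1/42) = 8.4% (two-sided exact 95% limit) or 1 − 0.05^(1/42) = 6.9% (one-sided). Section 3 also describes later work with months of familiarisation but gives no number of subjects, so no limit can be computed for prolonged wear.

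**The case against.** The strongest reply is that the protocol is silent and inconsistent, but does not forbid collection. Section 14 d exempts no event, and the heading of 14 e says all. Section 14 i gives contacts for serious adverse events and serious device effects, subjects are in contact throughout, and Section 12 commits to Good Clinical Practice. Comfort and fatigue are rated after each test task, the prosthetic evaluation questionnaire is completed at week 12, and QUEST 2.0 at week 24. The Investigator's Brochure, instructions for use and Risk Management File are attached but not shown, and no case-report form is shown. The content of Article 80(2) is not in the documents either.

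Much of this stands. A reader might infer that non-serious harm will never be collected, or that the trial is built to produce a clean safety record. The documents support neither. The first depends on the article's text and on papers not seen. The second fails because Article 80(2) events are to be recorded and notified, serious events have a route, and no safety analysis is stated that would yield such a conclusion. The event rates above are assumed, and the 0-of-42 limit depends on which experience the no-adverse-effects statement draws on.

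The reply does not repair Section 14. An empty list of exemptions is not a procedure, emergency contacts cover serious events only, and ratings after a test task or a satisfaction questionnaire do not capture what happened over 24 weeks. The missing definitions, the missing time limit and the contradiction on risk do not depend on the regulation's text.

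**Conclusion.** The point holds in a limited form. On the text alone, Section 14 defines none of its safety terms, ties its only commitment to record adverse events to a class whose content it does not state although the heading promises all events, sets no investigator-to-sponsor time limit, and contradicts Sections 4 c, 6.3 d and 14 h on risk.

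One further conclusion rests on the assumption that Article 80(2) means only authority-notifiable events. Other harm would then have no stated recording rule or enquiry for 24 weeks in either amputee group, and an absence of reported events could not be taken as an absence of harm. Over assumed risks of 5% to 20%, at least one such event among 20 LUNARIS users has a probability of 64% to 99%. These figures show only that events are likely to occur; they do not measure an error in the plan. The primary endpoint and its analysis are not affected. The recording rule should nevertheless be settled before enrolment, because unrecorded events cannot be reconstructed.

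**What to change.** - Put operative definitions of adverse event, adverse device effect, device deficiency and serious adverse event in 14 a to 14 c.
- State in 14 e to 14 g that all adverse events and device deficiencies, serious or not, are recorded in both amputee groups from allocation to week 24. Give a time limit for the investigator to report to the sponsor. Keep the Article 80(2) sentence for onward notification to authorities only.
- Add a short standard enquiry at the existing week-12 and week-24 visits and at withdrawal. It should include residual-limb problems, device malfunction and, given H1, falls. Tabulate the answers by group; with 20 per group and no randomisation this is descriptive.
- Reconcile the no-risk statements in 4 b and 14 a with 4 c, 6.3 d and 14 h.

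The cost is protocol wording, one case-report page and a few minutes per visit. Treatment, sample size and visit schedule do not change.

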#### f) Details of the process for reporting adverse events

We ensure that any event as referred to Article 80(2) will be fully recorded by the investigators, manufacturer or other parties, and immediately notified by the sponsor to all competent authorities (including FAMHP) by using the European form in a timely manner.

#### g) Details of the process for reporting device deficiencies

We ensure that any event as referred to Article 80(2) will be fully recorded by the investigators, manufacturer or other parties, and immediately notified by the sponsor to all competent authorities (including FAMHP) by using the European form in a timely manner.

#### h) List of foreseeable adverse events and anticipated adverse device effects

The LUNARIS® is a CE-marked medical device. Therefore, a risk analysis has been performed according to ISO 14971 to ensure that risks associated with the device are identified, evaluated and controlled.

The risk analysis shows that any residual risks which may be associated with the device are acceptable, when weighed against the benefits of the intended use to the lower-limb amputee, and compatible with a high level of protection of health and safety.

i) Emergency contact details for reporting serious adverse events and serious adverse device effects

The principal investigator can be contacted in case of emergency for the reporting of serious adverse events.

The manufacturer can be contacted in case of emergency for the reporting of serious adverse device effects.

j) Information regarding the Data Monitoring Committee

Data will be analysed by the co-investigator(s) and controlled by the principal investigator in assignment of the sponsor. The DMC is the Vrije Universiteit Brussel, [name].

### 15. Vulnerable population

Not applicable. Our population are healthy people with a lower limb amputation.

### 16. Suspension or premature termination of the clinical investigation

- a) Criteria and arrangements for suspension or premature termination of the whole clinical investigation or of the clinical investigation in one or more investigation sites

The clinical investigation will be considered as terminated when the proposed sample size is tested and is defined as the last visit of the last subject. As mentioned in the informed consent, subjects can stop or halt their participation at their convenience without any disadvantages.

The end of the clinical investigation or temporary study halt or early termination will be notified to FAMPH. In case of study end reporting this will be done within 15 days (and 24 hours if based on safety grounds). The study report will be submitted within one year of the end of the clinical investigation or within three months if early termination or temporary halt.

- b) Criteria for access to and breaking the blinding / masking code in the case of suspension or premature termination of the clinical investigation

The competent authorities shall be notified when the study will be terminated earlier than anticipated. Participation is voluntary, there can be no compulsion in any way. Even after subjects have signed, they can stop their voluntary participation.

- c) Requirements for subject follow-up and continued care

There is no follow-up plan considered since subjects perform the experiment with the novel investigated device or with the traditional prosthetic foot used in rehabilitation. Subjects can contact our department during and after the experiment for any further questions.

### 17. Publication policy

#### Statement A

The clinical investigation is registered in an open access database: ClinicalTrials.gov.

#### Statement B

The results of the clinical investigation will be published in an open access database: ClinicalTrials.gov. We are also aiming for a publication in a peer reviewed open access journal.

#### Statement C

Our publication policy is based on the 'Uniform Requirements for Manuscripts Submitted to Biomedical Journals': authorship credit is based only on (i) substantial contributions to conception and design, or acquisition of data, or analysis and interpretation of data; (ii) drafting the article or revising it critically for important intellectual content; and (iii) final approval of the version to be published. Conditions (i), (ii), and (iii) must all be met. Acquisition of funding, the collection of data, or general supervision of the research group, by themselves, do not justify authorship. Contributors who do not meet the criteria for authorship will be thanked in the acknowledgments section.

#### Statement D

The submitters of the present protocol proposal declare no financial or other conflicts of interest.

Trial results will be communicated to the general public through the publication of disseminated manuscripts published in scientific journals, and through conference presentations/posters. Authorship of these papers and presentations will only be granted to researchers that performed a substantial contribution to the scientific article. Public access will be granted to the entire protocol through the Clinicaltrials.gov registry. The statistical code and dataset will only be shared upon reasonable request, and the responsible data managers reserve the right to refuse such requests.

